### **3.8. Statistical Analysis**

SPSS version 25.0 will be used. Normality will be assessed using the Shapiro-Wilk test.

- Descriptive statistics: Mean  $\pm$  SD, median, and range.
- Group comparisons: Independent Samples t-test.
- Within-group comparisons: Paired Samples t-test.
- Effect size calculation: Cohen's d (small: 0.20-0.50, medium: 0.51-0.80, large:  $\geq 0.81$ ).
- Statistical significance:  $p < 0.05$ .

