#### 3.3. Participant Selection

##### Inclusion Criteria:

- Children aged 2–6 years with a genetically confirmed diagnosis of Type 1 SMA.
- Cobb angle between 20° and 40°.
- Undergoing or completed treatment with nusinersen and onasemnogene abeparvovec (OA).

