#### 3.4. Randomization & Blinding

Stratified randomization based on Cobb angle and age will be performed using Research Randomizer. Six strata will be created. A statistician blinded to group allocation will conduct the randomization. Assessors will be blinded.

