### **3.6. Outcome Measures**

Assessments will be conducted at baseline (pre-treatment) and after eight weeks of rehabilitation.

Primary Outcome Measure:

- Cobb angle will be assessed using supine spinal X-ray.

Secondary Outcome Measures:

- The basal upper-lower chest wall ratio will be evaluated using chest X-ray.
- Supine Angle of Trunk Rotation (SATRL and SATRU) will be measured using a scoliometer.
- Motor function will be assessed using the CHOP INTEND scale.
- Respiratory rate and SpO2 will be measured using pulse oximetry.
- Satisfaction with orthosis use will be evaluated using the QUEST 2.0 questionnaire.

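### The unadjusted t-test fixed for group comparisons gives up precision that ANCOVA on baseline Cobb angle and age would recover; how much depends on whether week-8 values or changes are tested

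*Protocol*

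**What the plan says.** Protocol section 3.8 lists one between-arm method, "Group comparisons: Independent Samples t-test", and one within-arm method, "Within-group comparisons: Paired Samples t-test". The second does not compare the arms. No covariate, stratum term or stratified test appears, and the section does not say whether the between-arm test uses week-8 values or change from baseline.

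Section 3.4 states "Stratified randomization based on Cobb angle and age will be performed using Research Randomizer" and "Six strata will be created". It gives no cut points, block size or other restriction within strata. Section 3.6 defines the primary outcome ("Cobb angle will be assessed using supine spinal X-ray") and the timing: "Assessments will be conducted at baseline (pre-treatment) and after eight weeks of rehabilitation". Section 3.3 admits Cobb angles of 20 to 40 degrees and ages of 2 to 6 years. Section 3.7 plans 18 evaluable children, 9 per group, at f = 0.65, alpha 0.05 and power 0.80, and recruits 24.

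**The concern.** A trial stratifies on a variable because it expects that variable to predict the outcome. If stratification works, the arms differ less on Cobb angle and age than chance alone would allow. An analysis without those variables still counts the variation they explain as random error. The computed standard error then exceeds the true one, and the true type I error falls below 5%. Even without that effect, leaving out a baseline that correlates with the outcome leaves explainable variance in the error term.

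With 9 to 12 children per arm there is little precision to spare. The unstated choice between week-8 values and change also matters for the primary outcome: at r = 0.7 it moves power by about 18 points (74% against 92%).

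**Working it through.** **Inputs from the protocol.** f = 0.65, so d = 2f = 1.30 for two equal groups; alpha 0.05, sidedness not stated; 9 per group; six strata from Cobb angle and age.

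**Assumptions.** Correlation r between baseline and week-8 Cobb angle of 0.5, 0.7 or 0.9, with equal variances at the two times; two-sided testing. For the size simulation: two Cobb by three age strata, permuted blocks within strata, a correlation of 0.2 between age and outcome, 3,000 runs.

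**1. The protocol's own figure.** The noncentrality of the t-test is d·√(n/2) = 1.30 × √4.5 = 2.76, with 16 degrees of freedom. Two-sided power is about 74%, and 80% is first reached at 11 per group (82.6%), or 22 children. A one-sided t-test gives 79.6% at 8 and 84.0% at 9 per group, which reproduces 18. A between-groups repeated-measures ANOVA with two measurements and correlation 0.5 also reproduces 18 (79.7% at 16 children, 84.8% at 18). The figure is therefore attainable, but not with a two-sided t-test on week-8 values.

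**2. Formulas for the three analyses.**
- Week-8 t-test: standardised effect d, whatever r is.
- Change-score t-test: d/√(2(1−r)), which is 1.30 at r = 0.5 and 1.30/√0.6 = 1.68 at r = 0.7.
- ANCOVA on baseline alone: noncentrality d²(n/2)/(1−r²) = 1.69 × 4.5/(1−r²), which is 7.605/0.75 = 10.1 at r = 0.5 and 7.605/0.51 = 14.9 at r = 0.7, on 1 and 15 degrees of freedom.

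The ANCOVA standard error is √(1−r²) times that of the week-8 test: 0.87, 0.71 and 0.44 at r = 0.5, 0.7 and 0.9. Relative to the change-score test it is √((1+r)/2): 0.87, 0.92 and 0.97.

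**3. Power at d = 1.30, 9 per arm, two-sided 5%.**

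| Analysis | r = 0.5 | r = 0.7 |
|---|---|---|
| t-test, week-8 values | about 74% | about 74% |
| t-test, change (simulated) | 75% | 92% |
| ANCOVA, baseline only (formula) | 84.5% | 95.0% |
| ANCOVA, baseline and age (simulated) | 81–84% | 92–94% |

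The formula ignores chance imbalance in the covariate, so it runs slightly high. At r = 0.9 the formula puts both the change-score test and ANCOVA on baseline above 99%.

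**4. True size under balanced allocation within strata, 18 children.** For the week-8 t-test the mean computed standard error is 0.466, 0.473 and 0.478 at r = 0.5, 0.7 and 0.9. The true standard deviation of the estimate is 0.428, 0.384 and 0.321. The ratios are 1.09, 1.23 and 1.49, and the true size is about 3%, 2% and 1%. For change scores the size is about 3–5%. ANCOVA on baseline Cobb angle and age has computed and true standard errors that agree closely (0.398 against 0.404; 0.328 against 0.328; 0.185 against 0.185) and a size near 5%.

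**5. Dependence on the allocation.** With strata explaining 40% of the variance (assumed), the unadjusted test on 24 children has size 1.2% under exact 2:2 allocation in six strata of four. After random loss of 6 of the 24 it is 2.0%. If allocation within strata is unrestricted it is 5.1%, so the conservatism disappears.

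**The case against.** The strongest reply is that the t-test may be meant for change scores. The objectives in section 2 speak of progression and changes, and section 4 expects slower progression in the orthosis arm. A change score already uses baseline, so a reader who infers that the plan ignores baseline Cobb angle goes further than the text allows. This stands. It removes most of the gain when r is 0.7 or more and leaves about 6–10 points at r = 0.5.

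A reader might also infer that the standard errors are too wide in any case. That needs allocation restricted within strata, which section 3.4 does not state, so the claim is conditional. Nor do the documents support saying that baseline dominates week-8 variance: they give no correlation, and r of 0.5 to 0.7 would mean 25% to 49% explained.

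Age may not be prognostic, and the term would then cost power. At d = 1.30 the loss is about 2–3 points. At a 1.0 SD difference, a simulation with age unrelated to outcome took ANCOVA from 77% to 73% at r = 0.7, no better than the change-score test, and from 61% to 57% at r = 0.5, against 51% for change. This also stands, as a modest cost.

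Finally, covariates are often left to a statistical analysis plan, and one may exist. But section 3.8 is not silent: it names a test, and that test makes no use of the stratification factors as covariates.

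**Conclusion.** The point holds as a matter of efficiency. The named test is valid: it is unbiased and does not inflate type I error, and nothing here suggests false positive results. It loses precision that the trial's own baseline data could supply.

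Against a week-8 t-test, ANCOVA on baseline Cobb angle and age raises power at d = 1.30 and 9 per arm from about 74% to 81–84% (r = 0.5) or 92–94% (r = 0.7). Against a change-score t-test the gain is about 6–10 points at r = 0.5 and negligible at 0.7 or above. Under balanced allocation within strata, the unadjusted test is also conservative: size about 3%, 2% and 1% on week-8 values at r = 0.5, 0.7 and 0.9, and about 3–5% on change.

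All of this rests on an assumed r and on two-sided testing. At r = 0.5 the lower end of the ANCOVA range is only one point above 80%, so adjustment should not be presented as a guarantee of the power in section 3.7.

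**What to change.** Replace the group-comparison line in section 3.8 with:

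*Primary analysis: ANCOVA of week-8 Cobb angle on group, with baseline Cobb angle and age as continuous covariates; report the adjusted mean difference in degrees with 95% CI.*

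For chest-wall ratio, SATR, CHOP INTEND, respiratory rate and SpO2, use the same model and add the outcome's own baseline to baseline Cobb angle and age, so that both stratification factors stay in every model. Leave QUEST 2.0 out: it rates orthosis use and has no meaningful pre-treatment value.

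The cost is wording only, and SPSS fits the model. It uses two degrees of freedom (three for secondary outcomes), against five for six stratum indicators. With 18 children the primary model keeps 18 − 2 − 2 = 14 residual degrees of freedom. If age is not prognostic, about 2–3 points of power are lost. The sentence also settles the choice between week-8 values and change.

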## **4. Expected Outcomes**

- The combination of spinal orthosis and trunk exercises is expected to lead to greater improvements in scoliosis progression, chest deformity, and motor function compared to trunk exercises alone.
- The Cobb angle is anticipated to show a slower rate of progression in the spinal orthosis group.
- Patients in the spinal orthosis group may demonstrate improved respiratory function due to enhanced chest wall stability.

- The CHOP INTEND scores are expected to improve more significantly in the spinal orthosis group due to better postural control and spinal alignment.

## 5. Dissemination Plan

Findings will be disseminated through peer-reviewed journal publications, conference presentations, and clinical practice guidelines for physiotherapists managing Type 1 SMA.

## 6. Conclusion

This study is the first to assess the combined effects of spinal orthosis and individualized trunk exercises on scoliosis progression and chest deformity in children with Type 1 SMA. The results will contribute to evidence-based rehabilitation strategies for managing scoliosis in SMA.

### **Funding**

This study was funded by the Scientific and Technological Research Council of Turkey (TUBITAK) under project code 323S007. The funders had no role in the study design, data collection, analysis, or publication decisions.

### **Competing Interests**

The authors declare no competing interests.
